#### Blinding

Blinding of research therapists in a therapy intervention study is not always feasible and patients are clearly aware that they are undergoing therapeutic interventions. Consequently, for this exploration of pedalling exercise, blinding of therapists and participants is not possible. However, the independent assessor of clinical outcome measures will be a trained therapist blinded to group allocation.

### Ethical considerations

Patients with communication deficit (particularly aphasia) are frequently excluded from stroke rehabilitation research, despite having potential for motor benefit. In clinical practice, however, stroke survivors with aphasia are included in motor rehabilitation. This protocol ensures that, providing patients can follow a single-stage command, they can participate. Thus the results of this trial will be applicable to clinical practice. In addition, the protocol addresses a frequent complaint from stroke survivors with aphasia; namely that they are not given opportunities to be involved in research.

However, in clinical practice as well as research, it is important to distinguish between language and cognitive communication impairment and close liaison with the clinical team, in particular the Speech and Language Therapy members, is essential. Before approaching a potential participant, the researcher will therefore discuss decision making capacity of individuals with the clinical team. If, as a result of their assessment, the clinical team's conclusion is that communication impairment is too great to allow an individual to give informed consent, then the researcher will not approach the potential participant. If the clinical team's conclusion is that informed consent is possible, albeit with the use of enhanced communication strategies, then the researcher will approach the potential participant.

Enhanced communication strategies will be used in this trial. These include the use of diagrams, charting information, repetition in a variety of ways and checking for understanding. In addition, information sheets and informed consent forms present information in a textual and pictorial form.

All potential participants will be given at least 24 hours (1 working day) to consider the information and ask questions. They will be encouraged to consult with others, outside of the research team, before making their decision.

All data will be encrypted and then stored on an lap top computer by the researcher before leaving the stroke unit. Data will be transferred onto a secure hard drive in the research laboratory. No names will be used in any recorded material except for the initial screening document. Participants will be anonymised with the use of study ID numbers.

The research study has received the **approval of the Essex 1Research Ethics Committee, UK (09/H0301/52)**.

### Participant inclusion criteria and recruitment process

Participants will be recruited from an acute stroke unit and, if necessary due to pressure on stroke beds, medical wards; in a University Hospital Trust. Consultant and therapy teams have agreed to support this trial.

Stroke survivors will initially be approached by a clinical team member responsible for their care, to check that they agree to speak to a researcher. If they agree, then a researcher will provide potential participants with verbal and written printed information about the trial. A video of the procedure for getting on and off the exercise cycle will also be available if patients wish to view it. A minimum of twenty four hours (1 working day) later, informed, signed consent will be sought. Those providing written informed consent will be participants in this trial. All potential participants will then be screened to check that they meet the study criteria, which are;

• adults aged 18+

• three to thirty days following a unilateral stroke resulting in unilateral muscle weakness with or without sensory deficit;

• fit to participate as assessed by a consultant-led medical team with resting oxygen saturations 95% or above, resting heart rate 90 beats per minute or less and systolic blood pressure of 100-160 mmHg

• score 0, 1 or 2 on the Functional Ambulation Categories [32]. Clinically, this means unable to walk; or need the help of two or more people; or require firm continuous or intermittent support of one person assisting with weight and balance;

• be able to sit unsupported for 30-seconds on the edge of a bed with feet on the floor.

• have sat out of bed in a chair or wheelchair at least once for a continual period of 15-minutes i.e. have appropriate sitting tolerance to participate in this cycling intervention;

• be able to follow a one-stage command i.e. sufficient communication, orientation and memory to participate in this cycling intervention;

• be independently mobile with or without an aid prior to the index stroke;

• have no co-existing pathology contributing to observed impairment in the paretic lower limb e.g osteoarthritis with associated knee deformity.

### Sample Size

This early phase trial is the first to use this equipment and with this participant group. Consequently there are no data to inform a power calculation. Sample size will therefore be based on practical considerations, using estimates of the number of participants we could expect to recruit within a 12 month time period. Using data from our previous trials of rehabilitation earIy after stroke [e.g [33]], we estimate a recruitment rate of two participants per month. Therefore, the sample size has been set at 24 participants.

### Intervention and Instrumentation

All participants will receive routine conventional physical therapy (CPT) as deemed appropriate by the clinical team. To enable replication of CPT we will record its content and dose (minutes of therapy) with a standardised schedule [34].

#### Control intervention

Participants allocated to the control group will receive CPT only as described above.

#### Experimental Intervention

Participants allocated to the experimental group will receive UP in addition to CPT. All experimental participants will be asked to pedal at 50 revolutions per minute (50 rpm) at a comfortable resistance whilst maintaining a heart rate of 85% or below their age-predicted maximum (i.e. less than 220-age ×0.85 beats per minute). If patients cannot achieve 50 rpm, the research therapist will be guided by their response in setting the maximum rpm. The mean rpm achieved will be recorded for each participant for each intervention session. It is anticipated that few patients this early after stroke will immediately manage ten minutes of pedalling, so the number of minutes pedalled, up to ten minutes, will be recorded.

Each intervention session will also involve recording: the pedal crank setting; the degree of reciprocal activation of antagonistic muscle groups (see measurement battery); the timing of onset and offset of activity in antagonistic muscle groups (see measurement battery); and the distance pedalled (m). This description of each intervention session will allow replication of the intervention and information on how to progress the intervention over time in subsequent clinical trials.

#### Instrumentation

Maintaining sitting balance early after stroke often requires substantial concentration and physical effort which may limit production of selective movement in the paretic lower limb. We have therefore adapted a standard exercise bike so that postural support for the trunk is provided if needed (figure 2).

**Figure 2 F2:**
[figure not shown]
**The modified exercise cycle**.

We have also incorporated a UniCam crank, an adjustment that can be applied to any commercially available exercise bike and which enables movement of the axis of the crank towards the centre of rotation of the bike pedal. This thereby reduces the circumference of the pedalling circle and reduces the required range of movement at the knee and hip, allowing patients who may have substantial lower limb weakness and/or limitations in the range of joint movement to still pedal.

EMG data will be collected using the *Datalink *system (Biometrics, UK). Muscle activity in quadriceps and hamstring muscles for each leg will be recorded using SX 230 (Biometrics, UK) preamplifiers. The preamplifiers connect to 4 analogue channels of the *Datalink *subject unit, which is connected to the base unit. Information from the base unit is collected on a lap top computer running the *Datalink *software system. Continuous EMG data will thus be recorded during pedalling.

The bicycle wheel is demarcated every 45 degrees using reflective tape. As the participant pedals, an LED sensor placed at a fixed point on the bicycle frame, is triggered as each of the eight markers passes (figure 3). This trigger creates a drop in voltage, creating a spike in the software. The spikes are recorded synchronously, via a digital channel on the *Datalink *subject unit, with the EMG data. This system allows for muscle activity to be related to the position of the pedal during the 360 degree turn.

**Figure 3 F3:**
[figure not shown]
**Diagrammatic representation of wheel demonstrating divisions**.

### Measurement battery

Baseline measures will be made before randomisation and outcome measures after the intervention phase has been completed (figure 1). Baseline measures consist of two sets: prognostic indicators and clinical efficacy. Outcome measures will consist of clinical efficacy measures only.

The ***participant characteristics ***to be recorded for all potential participants and participants will be: gender, age (years), type and site of the stroke lesion (liaison with medical team from scanning/clinical findings) and time since stroke onset at entry to the trial and at each set of study measures (days).

#### Clinical efficacy measures

As the primary aim of this pedalling intervention is to enhance ability to voluntarily contract paretic muscle, the primary measure enables assessment of impairment level change. The Motricity Index [35] is a simple measure that can be used easily in the clinical setting to assess the severity of motor impairment. It is also a significant predictor of ambulatory outcomes after stroke [30,36]. Hence it is a highly clinically relevant measure, as it provides a direct assessment of motor function that is correlated with eventual mobility outcomes.

To detect changes in muscle activity underlying participants' observed performance, EMG data will be employed. Therapists in the clinical setting frequently observe and record alterations in, for example, muscle strength and walking ability, but cannot accurately measure the biological changes in muscle activity that might contribute to changes in functional performance. In recording, processing and analysing at this level, the proposed trial will be able to evaluate biological change alongside frequently used clinical measures of recovery. This change in motor activity will be able to be detected earlier than if using clinical measures of movement performance alone.

Regaining mobility is a key goal for stroke survivors and independent mobility enables independence in other activities of daily living [9,30]. It is possible that, as pedalling exercise uses similar motor control patterns to those required for walking, UP after stroke might have a positive effect on ambulatory function. A measure of walking ability has therefore been included in this study. The Functional Ambulatory Categories (FAC) [32] has demonstrated sensitivity in stroke survivors who cannot walk at the beginning of their rehabilitation period, applicable to participants in this trial, who are not mobile at inclusion. This measurement of ambulatory function provides an assessment of an activity level change that is highly relevant after stroke and completes a spectrum of measures for this trial from body structure through function to activity.

##### Primary outcome

1. Ability to voluntarily contract paretic muscle

This will be measured by the Motricity Index (MI) lower limb section [35]. The MI is a widely used measure and has established validity and reliability for use after stroke [37]. It is an ordinal weighted scale with six measurement levels within each of three categories for the lower limb. The three categories are: ankle dorsiflexion, knee extension, and hip flexion. For each movement, a score of 0, 9, 14, 19, 25, or 33 is given, where 0 is no movement, 19 is full range movement against gravity not against resistance and 33 is normal power.

##### Secondary outcomes

2. Ability to walk independently

As measured by the Functional Ambulation Categories (FAC) [32]. This scale is designed to give detail on physical support needed by patients for walking, so has clinical relevance, and is easy to use. It has established validity and reliability for use after stroke [38]. It is an ordinal scale, patients scoring from 0-5, where 0 indicates a patient who is not able to walk or needs help of 2 therapists, and 5 indicates a patient who is independent in ambulation even on stairs.

3. Onset and offset of EMG activity of antagonistic muscle groups during pedalling

EMG activity will be recorded in quadriceps and hamstring muscles for each leg. Before getting on the bike, participants will have a small (37 mm × 18 mm) pre-amplifier applied to the front and back of their thigh on both sides, following skin preparation to minimise signal interference. Electrode position is known to be a vital factor in achieving accurate EMG information [39]. For this study, a single researcher will place the electrodes for each participant and for every session, using published guidelines [40]. When the participants are positioned comfortably on the bike, the leads from the pre-amplifiers will be connected as described in *instrumentation*.

Resting EMG activity will be recorded as a voltage at 1,000 Hz whilst the participant's foot is resting firmly on a box so that the leg is still and supported with the knee in 5-15 degrees of flexion, for 30 seconds. This will be undertaken for each leg. EMG data (voltage) will be collected continuously during pedalling for a minimum of 30 seconds at approximately 50 rpm.

Baseline EMG values will be calculated from the rectified, processed signal as the mean ± 3 SD (standard deviations) during the 30 seconds baseline data collection period. Onset of activity in each of the four muscle groups will be defined as the time point during the 360 degree turn at which EMG voltage exceeds the mean baseline value plus 3SD for 20 consecutive data points (20 ms). Offset of activity in each of the four muscle groups will be defined as the time point during the 360 degree turn at which EMG voltage falls below the mean baseline value minus 3SD for 20 consecutive data points (20 ms). The time point for onset and offset of muscle activity in each of the four muscle groups will also be recorded as a function of the position of the pedal during the 360 degree turn.

4. Reciprocal activation of antagonistic muscle groups (muscle activity) during pedalling

Rectified EMG data for each antagonistic muscle group will be analysed using Spearman's correlation coefficient. An r value of 1.0 indicates perfect positive correlation and therefore complete co-contraction, no reciprocal activation, of an antagonistic muscle pair. An r value of 0 indicates no correlation and therefore no relationship between EMG activity of an antagonistic muscle pair. An r value of -1.0 indicates a perfect negative correlation and therefore complete reciprocal activation of antagonistic muscle groups.

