## Aims

The driver for this proposed research is the hypothesis that UniCam crank-assisted upright pedalling (UP), used as an adjunct to conventional physical therapy, enhances recovery of lower limb motor function in stroke survivors with substantial paresis early after stroke. However, before this hypothesis can be tested in a phase III trial, it is important to establish whether there is sufficient evidence of benefit (clinical efficacy) to justify proceeding to subsequent larger trials and which stroke survivors are most likely to be able to participate in UP (prognostic indicators). Therefore, the aims for the current early phase clinical research study are:

1. Clinical Efficacy

To determine whether there is sufficient evidence for UP, balancing efficacy and potential adverse events (pain and fatigue), to justify proceeding to subsequent larger clinical trials; as assessed by:

a) ability to voluntarily contract paretic muscle;

b) production of reciprocal activation of antagonistic muscle groups during pedalling, similar to walking;

c) timing of onset and offset of activity in antagonist muscle groups during pedalling, similar to walking;

d) ability to walk independently.

2. Prognostic Indicators

To determine whether site of stroke lesion, trunk control ability, severity of lower limb paresis and/or ambulatory ability predicts ability to use UP within 30 days of stroke onset.

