Some exploratory studies have investigated the potential clinical efficacy of pedalling exercise after stroke [20,24,25] but the early findings of our systematic review (in progress) suggest that no trial has evaluated upright pedalling in a group of stroke survivors within one month of stroke onset. The potential challenges that early stroke survivors might face in taking part in this activity, such as safely sitting in an upright posture and taking part in repetitive exercise, have been addressed: firstly by using a modified exercise cycle, and secondly, by ensuring that physiological parameters and evidence of fatigue are monitored and recorded by the research team.

It is possible that our results might indicate none of the prognostic indicators are linked to the ability to pedal, and/or clinical efficacy of the intervention is not demonstrated. If this is the case, the risk of wasting valuable research resources on larger-scale trials, using the current indicators and measures, is minimised. However, interpretation of findings, whether negative or positive, will reflect the small sample size and early phase nature of this work.

A further novel aspect is that this study of pedalling exercise incorporates biological level measures, alongside more frequently used clinical, functional measures. EMG data from quadriceps and hamstrings will be recorded at baseline and outcome as well as at each pedalling session, providing evidence of any change at a biological level that might contribute to, and underpin, possible changes in functional measures. Using sessional EMG recordings will also allow analysis of whether pedalling is being achieved by the unaffected leg propelling the crank i.e with the use of compensatory strategies, or whether there are changes in recordable activity in the affected leg suggestive of recovery.

The control group will undergo conventional therapy only, and this will be quantified on a standardised treatment schedule, allowing for comparisons of amount and type of therapy across trial arms. Concern has been expressed that reporting of research into complex interventions often lacks sufficient detail on comparators [42]. The use of careful recording of conventional therapy in this trial will go some way towards addressing these concerns and might provide important information for potential dose-matching in later phase work.

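### EMG onset has no usable value for a paretic muscle that does not cross its resting threshold within the turn, so comparing onset angles between arms conditions on a response the treatment is meant to change

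*Protocol article*

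**What the plan says.** **Definition.** Item 3 under Secondary outcomes sets a resting reference: "Baseline EMG values will be calculated from the rectified, processed signal as the mean ± 3 SD", taken over 30 seconds of rest. "Onset of activity in each of the four muscle groups will be defined as the time point during the 360 degree turn", with the criterion that the signal "exceeds the mean baseline value plus 3SD for 20 consecutive data points (20 ms"). Offset is where the signal "falls below the mean baseline value minus 3SD for 20 consecutive data points (20 ms"). Pedalling is recorded "for a minimum of 30 seconds at approximately 50 rpm". The section gives no value or category for a muscle that never makes the crossing.

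**Use.** The Aims list, as part of clinical efficacy, "timing of onset and offset of activity in antagonist muscle groups during pedalling, similar to walking". Statistical Analysis compares follow-up measures between arms by independent t-test, or by a non-parametric analogue if normality cannot be assumed.

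**Population and treatment.** The working hypothesis is that pedalling "enhances recovery of lower limb motor function in stroke survivors with substantial paresis early after stroke". Clinical efficacy measures gives better voluntary contraction of paretic muscle as the main purpose of the intervention. Study procedure admits people to randomisation on a visual judgement that they can pedal; activity in the paretic muscle is not required. The Discussion says sessional EMG will allow analysis of "whether pedalling is being achieved by the unaffected leg propelling the crank".

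**The concern.** Onset exists only where the signal rises through the threshold inside the turn. Two patterns are possible in people who pass a visual pedalling test. In one, the paretic muscle stays at rest while the other leg does the work. In the other, the muscle stays above threshold for the whole turn. The first has no onset. The second has none, or is given the start of the turn as an arbitrary onset.

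A t-test or rank test needs a value for each participant on each muscle. If muscles without an onset are left out, the arms are compared only among muscles that fired in bursts at follow-up. Whether a muscle does so is what the treatment is meant to change, so the two subsets need not be comparable even though the arms were randomised. Suppose pedalling brings silent muscles into action and these are poorly timed. They then enter only the experimental average, while their counterparts in the control arm contribute nothing. A real gain in recruitment could look like worse timing in a result meant to inform the decision on larger trials.

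**Working it through.** **The plan's own figure.** There is no power calculation to reproduce. The sample size is a recruitment estimate: 2 per month × 12 months = 24, as stated. With 1:1 allocation (assumed) and every participant able to pedal, that is at most 12 per arm.

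**Recording.** At 50 rpm a turn lasts 60/50 = 1.2 s, so 30 s holds 30/1.2 = 25 turns. A run of 20 ms covers 360 × 20/1200 = 6 degrees.

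**The stated rules applied to simulated EMG** (1,000 Hz, rectified, 50 ms moving average, 23 scored turns; the smoothing is assumed):

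| Muscle | Upward crossing inside the turn | Offset at mean − 3SD | Offset if set at mean + 3SD |
|---|---|---|---|
| Silent | 0% | 0% | 0% |
| Weak burst (1.3 × rest) | 96% | 0% | 96% |
| Clear burst (5 × rest) | 100% | 0% | 100% |
| Continuously active | 0% (above threshold in 100% of turns) | 0% | 0% |

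The offset level was not met even for a clear burst. For unsmoothed rectified Gaussian noise, the mean is 0.798σ and the SD 0.603σ. Mean − 3SD is then 0.798 − 1.809 = −1.01σ, which a rectified signal cannot reach. Offset would therefore be missing for nearly all muscles, and selective loss is mainly an onset problem.

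**Size of the bias.** Let pc and pu be the shares of a given paretic muscle that are silent in the control and pedalling arms. Let d be the mistiming of newly recruited muscles relative to the rest, all in the same direction. Assume no other treatment effect and that no muscle is silenced by treatment. Among detected muscles,

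bias = d × (pc − pu)/(1 − pu).

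All inputs are assumptions, because the document gives none:

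- pc 0.20, pu 0.10, d 20: 20 × 0.10/0.90 = 2.2 degrees
- pc 0.30, pu 0.10, d 40: 40 × 0.20/0.90 = 8.9 degrees
- pc 0.40, pu 0.20, d 60: 60 × 0.20/0.80 = 15.0 degrees
- pc = pu, or d = 0: zero

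**Can the sign change?** Assume 60% of muscles always cross, with a timing error of 30 degrees in controls, and that pedalling improves this by 5 degrees. A further share q crosses only under pedalling, with error r. The expected difference among detected muscles is

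[0.6 × 25 + q × r]/(0.6 + q) − 30 (negative favours pedalling).

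| q | r = 40 | r = 60 | r = 80 |
|---|---|---|---|
| 0 | −5.0 | −5.0 | −5.0 |
| 0.10 | −2.9 | 0.0 | +2.9 |
| 0.20 | −1.2 | +3.8 | +8.8 |
| 0.30 | 0.0 | +6.7 | +13.3 |

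The sign flips once q/0.6 exceeds 5/(r − 30), that is 0.50, 0.17 or 0.10 for r = 40, 60 or 80. If newly recruited muscles are as well timed as control muscles (r = 30, q = 0.20), the difference is (15 + 6)/0.8 − 30 = −3.8 and the sign is kept.

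With 12 per arm, SD 15, q = 0.20 and r = 60 (20,000 simulated trials), about 9.6 pedalling and 7.2 control values are analysed per muscle. The estimate has the wrong sign in 66% of trials. With q = 0 it is wrong in 26%, from small numbers alone.

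**The case against.** **Exclusion is not stated.** A reader might infer that the protocol drops these participants. It does not say so. Exclusion is what results from the definition and the named tests together, and a full protocol or analysis plan might add a rule. This stands as a limit on the claim. The onset definition is nevertheless fixed in this document, and it yields no value for a silent muscle.

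**Silence is allowed for, not predicted.** The Discussion does not say that paretic muscles will be silent, and a crank driven mainly by the other leg does not imply silence. The simulation supports this caution, since a burst only 1.3 times resting amplitude was detected in 96% of turns. The document gives no frequency for either pattern.

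**The loss is per muscle.** Four muscle groups are scored, two in each leg, so a silent paretic muscle does not remove the participant from the other comparisons. A reading in which whole participants are lost is not supported.

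**Worse timing is not defined.** The outcome is a pedal position with no target angle, so early and late errors could partly cancel. The figures in degrees hold only if the errors run one way or are measured as deviation from a target.

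**Other measures cover part of this.** The Motricity Index scores voluntary contraction from no movement upwards, the Spearman correlation addresses co-contraction, and the recordings themselves show whether a muscle fires. That is correct. However, no stated EMG outcome compares the arms on whether the paretic muscle fires, and a correlation near zero could come from a silent muscle.

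**Early phase, secondary outcome.** The analysis does not claim to demonstrate efficacy definitively. This lowers the weight of the point but does not remove it, because the timing outcome serves a named efficacy aim.

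**Conclusion.** The point holds in a limited form. As defined, onset angle has no usable value for a silent or continuously active paretic muscle. A comparison restricted to detected onsets conditions on a post-randomisation response that the intervention is intended to alter. It can be biased, and under some assumptions the sign reverses. The document does not show that this will happen.

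The size cannot be derived from the document. The 2 to 15 degrees rests wholly on assumed gaps of 10 to 20 points and mistiming of 20 to 60 degrees in one direction. The 66% wrong-sign figure rests on assumed shares and errors, and should be read against 26% with no recruitment effect at all. The point concerns one secondary outcome, muscle by muscle; the primary outcome is unaffected. It is worth correcting before the EMG data are analysed.

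**What to change.** 1. For each paretic muscle, add a between-arm comparison of the percentage of recorded turns with a detected onset, for all randomised participants with a recording. Count silent turns and turns continuously above threshold separately. The participant is the unit, and the non-parametric option already in the plan can be used.
2. Report onset and offset angles among detected muscles as descriptive, with the number contributing in each arm.
3. Rank angles with no burst as the worst result only if two things are fixed first: a reference angle, so that the score is absolute deviation from a prespecified target, and a usable offset threshold. An angle within a turn is circular and has no worst end without such a reference.

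The cost is analysis wording. The same recordings serve, so no new measurement is needed. The downside is one more EMG summary and a main EMG result not expressed in degrees. The ranking in step 3 is not free either. In the simulated case with recruitment it pointed the wrong way in 23% of trials, against 66% for detected muscles only. With no recruitment it did so in 38%, against 26%. Participants with no follow-up recording remain missing under any of these measures and should be counted by arm.

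### EMG offset is set three SDs below the resting level, so crossing that limit would not mark the end of muscle activity

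*Protocol article*

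**What the plan says.** The rule is in the protocol article under Secondary outcomes, item 3.

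- **Resting recording.** "Resting EMG activity will be recorded as a voltage at 1,000 Hz whilst the participant's foot is resting firmly on a box", for 30 seconds, once for each leg.
- **Reference values.** "Baseline EMG values will be calculated from the rectified, processed signal as the mean ± 3 SD (standard deviations" over that resting period.
- **Onset.** The point in the turn at which "EMG voltage exceeds the mean baseline value plus 3SD for 20 consecutive data points (20 ms".
- **Offset.** The point in the turn at which the voltage "falls below the mean baseline value minus 3SD for 20 consecutive data points (20 ms".
- **Pedalling recording.** "EMG data (voltage) will be collected continuously during pedalling for a minimum of 30 seconds at approximately 50 rpm".

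Both events are also to be expressed as pedal position. Aim 1(c) depends on them: "timing of onset and offset of activity in antagonist muscle groups during pedalling, similar to walking". The Abstract names the same timing among the secondary outcomes, and the Experimental Intervention section has it recorded at every session. Nothing elsewhere in the article changes the offset rule.

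**The concern.** The two limits sit symmetrically around the resting mean, but muscle activity does not. A contracting muscle lifts the rectified signal above rest. When contraction ends, the signal comes back to rest. A limit above rest can therefore separate active from inactive. A limit the same distance below rest separates rest from something quieter than rest, which is not a state the muscle enters when it switches off.

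An analyst who follows the text would find no offset in most turns. Any offsets found would owe their number and position to chance or to the filter. Comparing the arms on offset timing would then compare missing values and artefacts.

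**Working it through.** The article gives no numerical result for this point, so there is no figure to reproduce. The check has an analytic part and a simulated part.

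**Inputs from the article (Secondary outcomes, item 3).** Sampling at 1,000 Hz; 30 s of rest; at least 30 s of pedalling at about 50 rpm; rectified and processed signal; limits at resting mean ± 3 SD; 20 consecutive points, which is 20 ms.

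**Step 1: rectified signal without smoothing.** Let the raw resting EMG be zero-mean Gaussian with SD s (an assumption). Its rectified version is half-normal:

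- mean = s × √(2/π) = 0.798 s
- SD = s × √(1 − 2/π) = 0.603 s
- offset limit = 0.798 s − 3 × 0.603 s = −1.01 s

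A rectified voltage cannot be negative, so this limit cannot be crossed.

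**Step 2: when the limit becomes positive.** Mean − 3 SD is above zero only if SD/mean is below 1/3. Without smoothing the ratio is 0.603/0.798 = 0.756. Smoothing lowers it. Relative to the resting mean the limit is 1 − 3 × (SD/mean), which is below 1 for any SD above zero. However heavy the smoothing, the limit stays under the resting level.

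**Step 3: simulation of the rule.** The article does not describe the processing, so a range was tried. Assumptions not in the article: Gaussian EMG in the 20–450 Hz band; a burst of 5 times rest for 40% of each turn; return to rest between bursts; moving averages or zero-phase low-pass filters. One turn at 50 rpm lasts 60,000/50 = 1,200 ms, so 30 s holds 25 turns, and 40 runs give about 1,000 turns.

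| Processing after rectification | SD/mean at rest | Offset limit ÷ resting mean | Onsets per turn | Offsets per turn, mean − 3 SD | Runs per turn below mean + 3 SD |
|---|---|---|---|---|---|
| None | 0.757 | −1.270 | 0.01 | 0.000 | 5.95 |
| Moving average 10 ms | 0.249 | 0.252 | 1.16 | 0.000 | 1.95 |
| Moving average 20 ms | 0.178 | 0.465 | 1.00 | 0.000 | 1.48 |
| Moving average 50 ms | 0.114 | 0.659 | 1.01 | 0.001 | 1.17 |
| Moving average 100 ms | 0.080 | 0.760 | 1.02 | 0.009 | 1.08 |
| Moving average 200 ms | 0.057 | 0.828 | 1.01 | 0.006 | 1.03 |
| Low-pass 50 Hz | 0.229 | 0.313 | 1.02 | 0.000 | 1.51 |
| Low-pass 20 Hz | 0.147 | 0.559 | 1.01 | 0.004 | 1.18 |
| Low-pass 10 Hz | 0.104 | 0.688 | 1.03 | 0.066 | 1.05 |
| Low-pass 6 Hz | 0.082 | 0.755 | 1.02 | 0.165 | 1.03 |
| Low-pass 3 Hz | 0.058 | 0.827 | 1.00 | 0.504 | 1.00 |

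**Step 4: reading the table.**

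- Once the signal is smoothed, onset is found about once per turn. The offset rule as written finds almost nothing with moving averages.
- With low-pass filters the offset count climbs from 0.000 to 0.504 per turn as the cut-off falls, although the simulated muscle is the same and never drops below rest. Those crossings are chance dips or filter undershoot.
- The last column counts every run of 20 points below the onset limit. With 50 to 200 ms averages it is close to one per turn. Values above 1 mean that some turns contributed more than one run, chiefly under light smoothing.

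**The case against.** The strongest reply is that the article describes a signal "calculated from the rectified, processed signal", not a merely rectified one. On an unsmoothed signal the 20-point onset rule fails as well (0.01 per turn), so some smoothing must be intended. The negative limit of −1.01 s then does not describe the signal to be used. This stands. A reader might infer that the offset rule can never be met; the text does not support that. On a smoothed signal the limit is positive and is sometimes crossed, and it could also be crossed if the resting recording contained tonic activity. What survives is narrower: such crossings do not mark the end of a burst.

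A reader might also infer that aim 1(c) as a whole is lost. It is not, because onset remains workable.

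A third tempting inference is that timing is confounded by cadence, since the Experimental Intervention section says "If patients cannot achieve 50 rpm, the research therapist will be guided by their response in setting the maximum rpm", or that angles around the turn are mishandled by t-tests. The article does not support this. It records pedal position as well as time and sets the EMG recording at about 50 rpm. The Statistical Analysis section does not say that milliseconds rather than angles are tested.

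Finally, the detection rates rest on assumed noise, burst size and filters, and a journal article may leave the processing to the full protocol. That is fair for the rates. It does not rescue the rule, because its reference, direction, multiplier and run length are all stated, and a limit below rest cannot identify a return to rest.

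**Conclusion.** The offset definition is wrong as written and should be fixed. It affects the offset half of secondary outcome 3 and of aim 1(c). Onset, the Motricity Index (primary outcome), the Functional Ambulation Categories and the Spearman measure of reciprocal activation do not use it.

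The core conclusion needs one assumption: a muscle that stops contracting returns to about its resting level. The figure of −1.01 s also assumes Gaussian noise and no smoothing. The per-turn rates hold only under the simulation's assumptions and show the pattern, not what this trial would observe.

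The point ranks as should-fix and no higher. It concerns half of one secondary outcome in a 24-participant early-phase trial that does not set out to demonstrate efficacy definitively. EMG is recorded continuously during pedalling, so offsets can be recomputed. The sentence may be a slip that the working analysis already avoids, but the text shown does not say so.

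**What to change.** Redefine offset as the first time after onset that the processed signal falls back below the resting mean plus 3 SD, the limit already used for onset, for 20 consecutive points. State that the same rectification and smoothing apply to the resting and pedalling recordings, and name the smoothing, because light smoothing leads to multiple detections in a turn.

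The cost is one corrected sentence in the protocol and one line in the EMG processing. No new data are needed, and recordings already made can be reprocessed.
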